**26. Analysis methods****26.a Primary analysis methods used for the primary outcome**

The primary analyses will be the estimation of the effect of the intervention on substance use disorders in high-risk youth in intervention conditions relative to their control counterparts, at the year 5 follow-up (48 months post-intervention). The odds ratio (OR) will be used as the measure of intervention effect for the binary substance use disorders outcome. To account for within-cluster (school) variance, intervention effects will be examined using hierarchical generalized linear modelling (HGLM; using the SAS program, Proc GLIMMIX) using a Bernoulli distribution for the binary primary outcome. The HGLM model will be two-levels, with students as the first level, and nested within schools (clusters) as the second level of the model.

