**26.b Supplementary analysis methods used for the primary outcome**

Similar to the primary analysis, supplementary analysis will be done on the binary primary outcome (substance use disorders) over all post-intervention time points (12 - 48 months), to estimate the effect of the intervention on substance use disorders in high-risk youth in intervention conditions relative to their control counterparts over the 5-year trial (i.e. growth in substance use disorders). To account for within-cluster (school) variance, intervention effects will be examined using HGLM, and the outcomes will be centered at the 12-month follow-up to allow for comparisons between groups post-intervention. The model will be three-levels, with time points as the first level, nested within students as the second level, nested within schools as the third level of the model. When significant effects are revealed on growth, analyses will be conducted (i.e. HGLM) testing intervention effects on onset of use at specific time points while controlling for cluster, using tests based on the Huber-White sandwich estimate of variance.

Supplementary analysis will also be done on the estimation of the effect of the intervention on the continuous value of the primary outcome measure (DEP-ADO scores) between control and intervention group, at the year 5 follow-up (48 months post-intervention). Effect will be analyzed using a mixed effect linear model to compute adjusted mean difference between arms along with their standard errors. The model will be two-levels, with students as the first level, nested within schools as the second level of the model. If there is a violation of distribution assumption on outcomes, appropriate transformation will be used.

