### **26.c Planned sensitivity analyses**

Sensitivity analyses will be implemented to examine plausibility of putative mechanisms underlying the effectiveness of the intervention as well as the interaction between intervention and participants' characteristics.

Sensitivity 1: Replace missing data for the binary primary outcome using multiple imputation (section 27.a).

Modification to protocol: The senior investigator never intended to report primary outcomes without replacing missing data. This was an oversight at the time of finalising the first analysis plan. We therefore have agreed to report primary outcomes after having replaced missing data using a full information method with 20 imputations (see 27.a). Therefore, this procedure will be followed for the primary and secondary analyses, and not only for Sensitivity analysis 1.

Sensitivity 2: Test effect in HR students who indeed received the intervention rather than mITT (ie Per Protocol analysis)

Sensitivity 3: Interaction between HR status and Intervention effect – does the intervention effect reveal itself at a population level?

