5. Some procedures not performed. We changed intervention adherence criteria: Overall 86% of HR students received intervention, but some schools had poor implementation which fell below our initial criteria for evaluation. We will control for adherence, rather than require a certain level of implementation. One school closed, but the school remained in the study, because they provided access to student information so that they could be followed individually. One school missed a follow-up survey in year 4 (due to natural disaster, flood) and instead completed two surveys 7 months apart in the final year: they are considered compliant and in the ITT.
6. **Deviation from planned statistical analyses:** when analysing this dataset, it became apparent that the Proc GLIMMIX method in SAS that is described in the analysis plan was not the most appropriate method to analyse this dataset, as this method required that an imputed dataset be generated in order to include all available data in the analysis. Due to the complex structure of this dataset, and the fact that data were missing at the individual and school level, multiple imputation as a method to manage missing data failed to converge, due to the fact that these models have difficulty managing high-dimensional models with correlated parameters. They either take very long to converge, or don't converge at all, especially for dichotomous outcomes. Very recently, the benefits of the Bayesian framework for managing multi-level data with missingness have been highlighted as potential solutions for social and health sciences. A number of solutions now exist using the STAN package in R. The MLM in Bayesian framework is especially useful when dealing with repeated measurements (e.g., when measurements are nested within participants) or when handling complex dependency structures in the data such as unequal sample sizes

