**The script used to create the primary outcome analysis is as follows:**

```

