##### model estimating linear growth over time #####
```

```
model_depado <- brm(Flagged ~ 1 + DEM_01 + Exp_Group + Language + year
+year:Exp_Group + (1|id+schoolnum),
data = cov_5,
family = bernoulli,
warmup = 1000,
iter = 3000,
cores = 4,
chains = 4,
seed = 123)
sum_model_depado<-summary(model_depado)
```

```

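### The SAP's primary-outcome script replaces the planned 48-month odds ratio model with two repeated-measures Bayesian models and does not extract the 48-month odds ratio

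*Combined protocol and SAP*

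**What the plan says.** SAP 26.a defines the primary analysis as the intervention effect on SUD in high-risk youth "at the year 5 follow-up (48 months post-intervention). The odds ratio (OR) will be used as the measure of intervention effect". On structure it says: "The HGLM model will be two-levels, with students as the first level", nested within schools. SAP Appendix 1 gives the primary outcome a single time frame, the fourth follow-up. SAP section 10 sizes the trial for that comparison, and section 16 waives multiplicity adjustment partly because there is one primary endpoint.

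The repeated-measures model has a different role. Under 26.b, "supplementary analysis will be done on the binary primary outcome (substance use disorders) over all post-intervention time points (12 - 48 months"), with three levels and outcomes centred at 12 months.

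The deviation list at the end of the SAP (item 6) then reports a change of method: "when analysing this dataset, it became apparent that the Proc GLIMMIX method in SAS that is described in the analysis plan" was not the best choice. Its main reason is that multiple imputation did not converge. It describes the change as a minor one, from a frequentist to a Bayesian multilevel model. After the sentence "The script used to create the primary outcome analysis is as follows" come two `brm` calls:

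- A linear-time model, beginning "model_depado <- brm(Flagged ~ 1 + DEM_01 + Exp_Group + Language + year", with a `year:Exp_Group` term.
- A model with `year_cat` and `year_cat:Exp_Group`.

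Both have random intercepts for student and school, and each is followed only by `summary()`.

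**The concern.** The plan and the script differ in more than the fitting method. The time frame changes from one visit to several. The structure changes from students within schools to visits within students and schools. The reported coefficients also answer different questions: an arm gap at the zero or reference year, and changes from it over time. Item 6 mentions none of this.

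Two models sit under one primary label without a rule for which one carries the conclusion. The SAP's case for no multiplicity adjustment relies on a single primary endpoint, and two models with several arm terms each weaken that protection.

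At stake is the headline result. A slope and a year-5 contrast can give different answers, and the SAP committed only to the second. By item 6's own account the change came while the dataset was being analysed, and SAP section 4 says that analyses are not blind to randomised group.

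**Working it through.** **1. The plan's own figure.** Section 10 gives a 10% v 5% SUD rate, 50 students per school, k = 0.35, 80% power and a 2.5% error rate. A 2.5% one-sided rate is the same as the two-sided 5% of section 15. The unmatched cluster formula for proportions is

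c = 1 + (z_α + z_β)² × [p0(1−p0)/m + p1(1−p1)/m + k²(p0² + p1²)] / (p0 − p1)²

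- Bracket: 0.09/50 + 0.0475/50 + 0.1225 × 0.0125 = 0.00180 + 0.00095 + 0.00153 = 0.00428.
- c = 1 + 7.849 × 0.00428125/0.0025 = 14.44, rounded up to 15 per arm.

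This reproduces the stated 15. The trial was therefore sized for a comparison at one time point. The planned odds ratio is (0.05/0.95)/(0.10/0.90) = 0.474.

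**2. What each model's coefficients mean.**

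- Linear model: `Exp_Group` is the arm log odds ratio where `year` = 0, and `year:Exp_Group` is its change per year. The 48-month log odds ratio is `Exp_Group` + T × `year:Exp_Group`, where T is the value of `year` at 48 months. It is right only if the arm gap and the time trend are linear on the logit scale.
- Categorical model: the 48-month log odds ratio is `Exp_Group` + the year-5 interaction, with no linearity assumption.

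The script requests neither sum. It does not state how `year` is coded or which waves `cov_5` holds.

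**3. Can the slope model and the year-5 contrast differ?** Assume control rates of 1% at baseline and 2, 4, 7 and 10% at 12 to 48 months. Fit the printed time-by-arm terms to expected proportions, with equal weight per visit and arm, no random effects or other covariates, and `year` = 0 at the first wave.

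| True pattern | Waves | True 48-month OR | exp(`Exp_Group`) | exp(`year:Exp_Group`) | Linear model's implied 48-month OR |
|---|---|---|---|---|---|
| Effect only at 48 months | 12–48 | 0.474 | 1.249 | 0.780 | 0.592 |
| Effect only at 48 months | 0–48 | 0.474 | 1.326 | 0.827 | 0.620 |
| Constant from 12 months | 12–48 | 0.474 | 0.475 | 0.998 | 0.473 |
| Constant from 12 months | 0–48 | 0.474 | 0.643 | 0.914 | 0.448 |
| Full at 12, none at 48 months | 12–48 | 1.0 | 0.491 | 1.262 | 0.987 |

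Check of row 1: 1.249 × 0.780³ = 0.593, which agrees with 0.592 up to rounding. In every scenario the categorical model returned the true 48-month odds ratio as the sum of its two coefficients. With 12–48 month data its last interaction alone did not: it was 1.00 under a constant effect.

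**4. Scale.** A student random intercept makes the odds ratio conditional on the student. Holding the risks at 10% v 5% and integrating over a normal intercept, the conditional odds ratio is 0.474, 0.446, 0.366 and 0.276 for a student SD of 0, 1, 2 and 3. The SDs are an assumed range, since the documents give none.

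**The case against.** The best defence is that the planned quantity is not lost. The categorical model holds it, and one extra line would report it. If the reference wave is a baseline with no arm difference, the printed year-5 interaction already equals it. If `year` were coded 0 at 48 months, `Exp_Group` in the linear model would be a model-based version of it. This stands: the fault is failure to extract and designate the quantity, not failure to estimate it.

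A reader might also infer several stronger things that the documents do not support:

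- *The growth model was chosen after the data were seen.* Growth modelling is in protocol 2.16 and SAP 26.b. What came during analysis is the Bayesian form, with repeated-measures models in the primary role. Item 6 gives a technical reason, and nothing says that the choice followed results or that the conclusion rests on the slope.
- *A constant effect would read as no effect.* The slope would be null, but `summary()` would print an `Exp_Group` odds ratio of about 0.475 beside it.
- *The 5% test has no Bayesian counterpart.* The `brms` summary gives 95% intervals by default. What is missing is a statement of which interval decides.
- *The missing imputation term is itself the error.* SAP 26.c does say "We therefore have agreed to report primary outcomes after having replaced missing data", but item 6 openly withdraws imputation. A model fitted to all observed visits can handle outcomes missing at random without it, as a likelihood fit would.
- *The registered question goes unanswered.* The documents give only a registration number, so the comparison can be made only with the SAP.

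A conditional odds ratio is a different scale, not a mistake. The 26.a model is itself conditional on school.

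**Conclusion.** The concern holds in this form. The SAP's primary-outcome script substitutes two repeated-measures Bayesian models, adopted during analysis, for the planned two-level comparison "at the year 5 follow-up (48 months post-intervention"). It promotes a supplementary structure, gives no rule for choosing between the models, and does not report the 48-month odds ratio that the second model can supply. Item 6 understates the change.

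The size depends on how the effect develops. If it appears only at 48 months, a true 0.474 becomes 0.59 to 0.62 under the linear model. If it is constant or fades linearly from 12 months, the model's implied 48-month value is close to the truth (0.45 to 0.47 against 0.474, and 0.99 against 1.0), though the slope alone says something else. These figures rest on assumed control rates and a simplified fit, so they show that the answers can differ and do not estimate a bias in this trial. Its actual discrepancy cannot be computed because the documents contain no outcome data.

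**What to change.** - Name the year-5 arm contrast as the only primary result. Take it from the categorical-time model as `Exp_Group` plus the year-5 interaction, with its 95% interval.
- Also report it standardised to 48-month risks in each arm and a marginal odds ratio, so that it can be compared with the planned 10% v 5%.
- State how `year` is coded and which waves are in `cov_5`.
- Label the linear growth terms supplementary, as in 26.b.
- Declare in item 6 that both the Bayesian form and the repeated-measures structure of the primary analysis are post hoc.
- Report a likelihood fit of the same contrast beside the Bayesian one.

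The cost is revised SAP wording, one contrast and standardisation step on the existing categorical fit, and one further model run. No new data are needed.

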Primary outcomes are on the intent to treat sample of youth who meet high risk (HR) personality criteria. To account for within cluster (school) variance, intervention effects will be examined using hierarchical generalized linear modelling (HGLM; using the program HLM 6) [111, 112] using a Bernoulli distribution for the binary primary outcome. Secondary outcome variables will be centred at the 12-month post-test to allow for comparisons between groups (intervention vs. control) after the intervention, and growth terms will be used to detect prevention effects on growth of onset of target behaviour over four years. For the three drinking outcomes, unconditional models from previous trials revealed that more than 10% of systematic variance existed at the between-school level (25-27%), therefore, HLM with robust standard errors will be used to assess intervention effects on the 12-month intercept and growth in drinking from 12-48 months [111]. When significant effects are revealed on growth, STATA (StataCorp, College Station, TX) will then be used to conduct logistic regression analyses testing intervention effects on onset of use at specific time points while controlling for cluster, using tests based on the Huber-White sandwich estimate of variance [110]. The illicit drug use outcome, problem drinking outcomes and cognitive outcomes are not expected to have high inter-class correlations [29]; HGLM will be used to conservatively assess these outcomes, nevertheless. We will also report cluster-level analyses in which individual-level variability is removed and analyses are conducted at the school-level, comparing mean outcomes for intervention (n=15) and control schools (N=15) using one-way repeated measures design with time as repeated measures and intervention as a fixed independent variable following recommendations by [113]. Path analyses will investigate mediational role of substance use and cognitive outcomes risk for addiction.

*2.17 What is the proposed frequency of analyses?*

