or missing data. Many statistical packages are developed to fit MLMs but their functionality is limited to the mean of the response distribution, with other parameters of the response distribution, such as the residual standard deviation in linear models, assumed constant across observations. However, when sample sizes or variances change over time, or when missing data occur at different levels in the structure of a dataset, a maximal varying effect structure is needed and many approaches will give aberrant estimations of the correlation between varying effects. While the Proc GLIMMIX provides estimators to correct for this instability, it is generally agreed that Bayesian approaches are better suited to solve this type of problem, especially for dichotomous outcomes with sparse distribution (few non-zeros). It is also preferred to not have to impute datasets in order to replace missing data, which the Bayesian approach allows. Therefore, a slight deviation from the original analysis strategy involved moving from a frequentist to a BayesianMLM model. STAN uses the brms package and supports diverse distributions and link functions, allowing for multiple grouping factors each with multiple group-level effects. It also allows for autocorrelation of the response variable, user defined covariance structures, an flexibleand explicit prior specifications.

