##### model with categorical time variable #####
```

```
cov_5$year_cat=as.factor(cov_5$year)
```

```
model_depado_cat <- brm(Flagged ~ 1 + DEM_01 + Exp_Group + Language +year_cat +
year_cat:Exp_Group + (1|id+schoolnum),
data = cov_5,
family = bernoulli,
warmup = 1000,
iter = 3000,
cores = 4,
chains = 4,
seed = 123)
sum_model_depado_cat<-summary(model_depado_cat)
```

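### The primary-outcome code gives schools a random intercept only, so its time-by-arm intervals are too narrow if schools differ in their trends

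*Combined protocol and SAP*

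**What the plan says.** The deviation note at the end of the SAP replaces PROC GLIMMIX with Bayesian multilevel models and introduces the code with "The script used to create the primary outcome analysis is as follows". Two models follow. The linear-growth model contains "year:Exp_Group + (1|id+schoolnum"; the categorical-time model contains "year_cat:Exp_Group + (1|id+schoolnum". In both, student and school each have a random intercept. Neither model has a school slope for year, a school-by-year effect or a robust variance.

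The same note argues that, with missingness at several levels or sample sizes that change over time, "a maximal varying effect structure is needed and many approaches will give aberrant estimations of the correlation between varying effects".

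Other parts of the plan bear on the point:

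- SAP section 10 states that the school is the unit of randomisation and plans with a between-school coefficient of variation k of 0.35 at Grade 11.
- SAP section 26.a places the primary effect "at the year 5 follow-up (48 months post-intervention). The odds ratio (OR) will be used as the measure of intervention effect".
- SAP section 26.b (supplementary analyses) describes growth thus: "The model will be three-levels, with time points as the first level, nested within students as the second level, nested within schools". No school-level slope is stated. It also plans sandwich-based tests at single time points.
- Protocol section 2.16 says, for drinking outcomes, that "HLM with robust standard errors will be used to assess intervention effects on the 12-month intercept and growth in drinking from 12-48 months". It adds school-level comparisons of 15 against 15 schools.

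**The concern.** When arms are assigned by school, a difference between arms in change over time has to be judged against how much that change varies from school to school. A school random intercept covers differences in level only. With no school-level time term, the model sets the between-school variance of the trend to exactly zero. Any real school differences in trend are then left out of the standard error of the time-by-arm terms.

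At stake is the width of the interval on the primary outcome in a trial with about 30 schools. The code's formula also does not match the reason given for adopting this method, since it fits the smallest varying-effect structure that still recognises schools.

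**Working it through.** **1. The plan's own figure.** Inputs from SAP section 10: 10% versus 5%, 50 students per school, k = 0.35, 80% power, error rate 2.5%.

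Schools per arm = 1 + (z_a + z_b)² × [p0(1−p0)/m + p1(1−p1)/m + k²(p0² + p1²)] / (p0 − p1)²

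- Bracket: 0.09/50 + 0.0475/50 + 0.1225 × 0.0125 = 0.00428.
- With 2.5% one-sided (5% two-sided): 1 + (1.960 + 0.842)² × 0.00428/0.0025 = 14.44, so 15. This reproduces the plan, and k = 0.35 is its working value for between-school variation.

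**2. From k to a school slope SD.**

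- At 10% prevalence the school SD is 0.35 × 0.10 = 0.035, or 0.035/(0.10 × 0.90) = 0.39 on the marginal logit scale.
- The fitted model is conditional on student effects. With student SD σ, the usual logistic-normal scaling multiplies by √(1 + 0.346σ²), where 0.346 = (16√3/15π)². For σ = 2 this is 1.54, giving 0.39 × 1.54 = 0.60.
- If all of it builds up linearly over four years, with slopes uncorrelated with intercepts, the slope SD is 0.60/4 = 0.15 logits per year. This is a cap: any part present at baseline lowers it.
- σ is not in the documents. The cap is 0.11 for σ = 1 and 0.20 for σ = 3.

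**3. Effect on the intercept-only model.** Setting: 31 schools (SAP section 20), the 15 intervention-school sizes in SAP Table 2 (total 709, mean 47.3) and 16 control schools of 47 (assumed), five waves. Assumptions not in the documents: prevalence 1.5% at baseline, σ = 2, retention 85%. Prevalence of 10% at Grade 11 is the plan's figure.

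With H the model's information matrix and J the extra score variance from school slopes, the true variance is H⁻¹ + H⁻¹JH⁻¹. If f is true SE over model SE, the false-positive rate at nominal 5% is 2Φ(−1.96/f). Null trials were also simulated and fitted by approximate maximum likelihood with Wald tests.

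| School slope SD (logits/year) | f, interaction | Rate by formula, interaction | Simulated, interaction | Simulated, 48-month contrast |
|---|---|---|---|---|
| 0 | 1.00 | 5.0% | 3.6% | 3.0% |
| 0.075 | 1.03 | 5.8% | 4.3% | 4.0% |
| 0.106 | 1.07 | 6.6% | 4.6% | 4.3% |
| 0.15 (cap at k = 0.35) | 1.13 | 8.2% | 5.9% | 6.3% |
| 0.20 (simulated at 0.21) | 1.22 | 10.8% | 9.9% | 6.6% |
| 0.30 | 1.45 | 17.6% | 15.1% | 8.1% |

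The first four rows used 1,500 simulated trials each and the last two 800. The last two simulated rows need Grade 11 variation of k = 0.5 and 0.7, above the plan's value. The simulated fit is conservative (3.6% where 5% is expected), so its figures lean low.

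**4. Sensitivity, by formula.**

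- Four post-baseline waves only: 7.1% at slope SD 0.15.
- Grade 11 prevalence of 20%: 8.9% at 0.15.
- Rate at the cap for σ = 1, 2, 3: 7.4%, 8.2%, 9.0%.

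**5. With a school random slope added.** The simulated rate for the interaction is 3.3% to 4.3% in every scenario, and for the 48-month contrast 2.0% to 5.6%. The interaction's median SE grows by a factor of 1.00 to 1.07 at k = 0.35, 1.18 at slope SD 0.21 and 1.35 at 0.30.

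**The case against.** The best defence has four parts.

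- **The slope variance may be zero.** The documents report none, and at zero the model is calibrated. This stands, and it makes the point conditional. But the code fixes the variance at zero without looking, and the documents give grounds for doubt: completion of both sessions ran from 51% to 100% across intervention schools (SAP Table 2), and SAP section 26 says schools differ markedly in immigration status, which it calls strongly protective.
- **The interaction is not the named test.** This also stands: SAP 26.a makes the 48-month odds ratio primary and growth supplementary. The printed code, however, stops at a model summary, computes no 48-month contrast and does not give the coding of year. The contrast is affected too, though less than the interaction at slope SDs of 0.2 and above.
- **Other analyses protect against this.** The protocol's school-level comparisons and the SAP's sandwich tests at single time points are useful, but they are separate analyses. They do not correct the interval from this model.
- **The remark about a maximal structure is general.** It justifies the change of method and is no evidence that slope variance exists. Agreed; it shows only that text and code disagree.

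A reader might also infer much larger inflation from the intraclass correlation of 0.09 in protocol section 2.11. At 10% prevalence that implies k = √(0.09 × 0.09)/0.10 = 0.9, and so a slope SD of up to 0.15 × 0.9/0.35 = 0.39, for which the formula gives about 25%. The documents do not support this as the expected size. The figure is for problem drinking in an earlier trial, it describes variation at one time, all of it would have to arise after baseline, and the sample size rests on k = 0.35, which implies a correlation of only 0.035²/0.09 = 0.014.

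**Conclusion.** The omission is real in both models and its direction is clear: if schools differ in their trends, the time-by-arm intervals are too narrow. It cannot be said that they are too narrow, or that the error rate exceeds 5%, because the slope variance is unknown.

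Within the plan's k = 0.35 and the assumptions above, the false-positive rate is 5% to about 8% for the interaction and about 6% for the 48-month contrast (by a simulation that leans low). The interaction reaches 10% only from a slope SD of about 0.2 per year. A negative correlation between school intercepts and slopes would allow larger slopes at the same k. The figures are likelihood-based Wald rates for the linear model. They approximate the Bayesian intervals, and the categorical model was not simulated.

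This should be fixed. It does not by itself invalidate the primary result.

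**What to change.** - **Linear model:** replace the random part by `(1|id) + (1 + year|schoolnum)`.
- **Categorical model:** use `(1|id) + (1|schoolnum) + (1|schoolnum:year_cat)`.
- **Report** the school slope SD, or the school-by-year SD, with its interval, so that readers can see whether the term matters.
- **Primary contrast:** state the coding of year and compute the 48-month odds ratio of SAP 26.a explicitly from the extended model.
- **Growth models** in SAP 26.b (supplementary) and 26.c (secondary outcomes): specify the same school-level term, on which both sections are silent.

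The cost is one line per model, a longer run time and somewhat wider intervals: 0% to 7% on the interaction's SE at the plan's between-school variation, and more only where schools diverge more.
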